## Abstract

**Background:**

High blood pressure is a major public health problem in low- and middle-income countries. Low-sodium salt substitute (LSSS) is a promising population-level blood pressure-lowering intervention requiring minimal behavioral change. The optimal method of delivering LSSS to individuals, however, is currently unknown. Community health workers (CHWs) have successfully been used to implement health interventions in Bangladesh and may provide a venue for the dissemination of LSSS.

**Methods:**

We aim to conduct a cluster-randomized controlled trial involving 309 households in rural Bangladesh previously identified and characterized by the BRAC James P Grant School of Public Health, BRAC University (BRAC JPGSPH). These households will be randomly assigned to three arms: (1) control, i.e., no intervention; (2) information only, i.e., community health workers will provide basic information on high blood pressure, the health consequences of excessive salt consumption, and feedback to the participant on the likely quantity of salt s/he consumes (estimated using a questionnaire); (3) free LSSS arm: the same information as in arm 2 will be provided, but participants will receive 6 months of free low-sodium salt along with education on the benefits of LSSS. One male and one female adult (age ≥ 18 years) in each household will be invited to participate, the exclusion criteria being households with members known to have high serum potassium levels, are taking medications known to elevate potassium levels (e.g., ACE inhibitors, ARBs, potassium-sparing diuretics), are already taking potassium supplements, or those who have known kidney disease or abnormal serum creatinine at baseline. The primary endpoint will be blood pressure at 6 months post-intervention.

**Discussion:**

Recent large clinical trials of LSSS in China and India have shown not only blood pressure improvements, but also stroke, major cardiac event, and all-cause mortality reductions. Nevertheless, how to best translate this intervention to population-level effectiveness remains unclear. Our study would test whether a community health worker-based program could be effectively used to disseminate LSSS and achieve measurable blood pressure benefits.

**Trial registration:**

ClinicalTrials.gov NCT05425030. Registered on June 21, 2022.

**Supplementary Information:**

The online version contains supplementary material available at 10.1186/s13063-023-07518-3.

## Introduction

### Background and rationale 

High blood pressure, which is already more common in low- and middle-income countries (LMICs) than in high-income countries, is responsible for a significant burden of cardiovascular diseases (myocardial infarctions (MIs, i.e., heart attacks), strokes), and renal failure in these settings [1, 2]. Over the past several decades, cardiovascular disease has become the leading cause of mortality in LMICs, and this problem is only expected to increase in LMICs such as Bangladesh due to rapidly shifting demographic trends including population aging, dietary changes, and sedentary lifestyles [3–5]. Regrettably, LMIC public health systems are not prepared to prevent and control the epidemic of cardiovascular diseases. Furthermore, those living in poor countries usually lack the financial means to treat the devastating sequelae of cardiovascular risk factors [6, 7].

Blood pressure reduction represents an attractive target for intervention, as it is associated with heart attacks and stroke in a log-linear fashion down to a systolic and diastolic BP of 115/75 mm Hg [8]. This implies that reductions in blood pressure in the general population, rather than just among those above the clinical threshold for hypertension, would lead to important health benefits. Despite the availability of proven, effective medications, reducing blood pressure in LMICs is proving difficult, however, for a number of reasons. These include problems with early detection of elevated blood pressure, ensuring that antihypertensive medications are readily available and affordable to patients, and convincing patients to take (and frequently pay for) medications long-term for an asymptomatic disease [9]. Furthermore, nonpharmacologic interventions for lowering blood pressure such as increasing people’s physical activity and improving their dietary habits to reduce sodium intake (the primary nutritional driver of hypertension) have generally proven to be difficult even in high-resource settings. This has been due to several causes including a persistent and prevalent “obesogenic” environment and overemphasis on medical procedures and drug therapy (over lifestyle and behavioral interventions). Moreover, the mental fatigue of sustaining healthy habits and social acceptance of maladaptive behaviors lead to poor durability of lifestyle changes after such interventions are introduced [10, 11].

Given these issues, low-sodium salt, a compound in which 25 to 75% of the sodium chloride (NaCl) is replaced by potassium chloride (KCl) and/or magnesium sulfate (MgSO_4_), is an attractive intervention for blood pressure reduction, as it avoids several of the previously-mentioned issues of lifestyle change challenges:

First, little behavior change is needed: As long as the non-sodium portion of the salt does not exceed one-third of the product, the taste of the low-sodium salt product is indistinguishable from regular salt, and in some studies in LMICs, blinded subjects preferred the low-sodium salt [12–14]. It can be used in the same manner as regular salt in cooking and seasoning foods by usual cultural practices in such settings [13].

Furthermore, little additional cost is imposed upon the consumer: KCl and MgSO_4_ are cheap, readily-available minerals/nutritional supplements (with their own health benefits) with similar costs as regular salt.

Finally, no special technologies or advanced medical oversight for intervention delivery are needed: No physician supervision, special preparation equipment, or monitoring systems are necessary for the use of low-sodium salt by the target audience [15].

Overall sodium intake is also often higher in LMICs than high-income countries—for example, the average daily salt intake in German adults was estimated to be 8.4–10 g/day [16]. In adults in Bangladesh, it may be as high as 17 g/day [17]. A large proportion of salt intake in LMICs tends to be from home-prepared meals rather than ready-made processed foods: Compared to high-income countries, a greater proportion of food consumed in LMIC settings (including Bangladesh) is prepared within the home, particularly in rural areas, thus increasing the potential benefits of the intervention.

Recent large clinical trials of LSSS in China and India have shown not only blood pressure improvements, but also stroke, major cardiac event, and all-cause mortality reductions in randomly-assigned users [18, 19]. Despite these impressive findings, there is a gap in the literature, as such RCTs have relied upon trial staff to provide LSSS free of charge to participants as part of standardized experimental protocols. Such personnel are not health workers who would otherwise be available to existing LMIC health systems. As such, how to best translate the LSSS intervention to population-level effectiveness in such settings remains unclear. Innovative delivery mechanisms such as educational campaigns and directed provision by local health workers have been effectively used in LMICs to disseminate other behavioral interventions in primary care [20–22]. Additionally, community health workers are increasingly proving to be a powerful resource for the delivery of care for both noncommunicable diseases and primary care in LMICs [20, 22, 23]. They are cost-effective, respected in their home communities, and fill a much-needed healthcare personnel gap in rural/remote regions of countries where nurse and physician staffing cannot be reliably guaranteed [24–27]. As such, we hypothesized that CHWs may represent a promising means for spreading knowledge and acceptance of LSSS in LMIC settings, bridging the gap in knowledge between idealized RCT results and a delivery mechanism for this population-level intervention.

In Bangladesh, the setting of this proposed study, there exists a robust CHW network which has successfully delivered many public health interventions in a variety of regional and local contexts [23, 25–27]. Therefore, findings from our RCT would be immediately actionable through extant CHW programs within both the study community as well as the country at large.

### Objectives 

To determine the effect on blood pressure of a community health worker-based education program providing information about ways to reduce one’s salt intake and the health benefits of doing so.To determine the effect on blood pressure of a community health worker-based program providing low-sodium salt directly to households in addition to information about ways to reduce one’s salt intake and the health benefits of doing so.

### Trial design

The design of this RCT is a cluster-randomized, parallel-group superiority study. The unit of randomization will be a standard household, which is defined by the WHO STEPS Noncommunicable Disease Risk Factor Survey as “a dwelling in which persons, either related or unrelated, live together and take food from the same kitchen.” Participants will be randomized into one of three study arms as further detailed below:

## Methods: participants, interventions, and outcomes

### Study setting

Our study setting is in Rampur Union, Parbatipur, a rural/semi-rural sub-district in Dinajpur District (Rangpur Division), in northern Bangladesh. Within Parbatipur, BRAC has assessed approximately 8000 households for noncommunicable disease risk factors as part of a larger Wellcome-trust funded multinational biobank (involving those living in Bangladesh, India, Pakistan, and Sri Lanka) to better understand the patterns and determinants of cardiovascular health in South Asian people in a cross-sectional analysis [28, 29]. To avoid spillover, every fifth household will be approached during the enrollment phase to minimize neighborhood effects. Specifically, the areas of Uttor Basupara, Basupara, and Mondolpara, which are adjacent to one another with a similar socio-economic makeup within Rampur Union, will be approached for enrollment.

### Eligibility criteria

One male and one female adult (age ≥ 18 years) in each study household will be invited to participate. The exclusion criteria are subjects known to have high serum potassium levels, are taking medications known to potentially induce hyperkalemia (potassium-sparing diuretics, Angiotensin-converting enzyme (ACE) inhibitors, Angiotensin II receptor blockers, digoxin), are already taking potassium supplements, or those who have known kidney disease at baseline. Additionally, all adults residing in the selected households initially screened for intervention will undergo serum creatinine testing, with those with estimated glomerular filtrate rate (eGFR) values < 60 ml/min/body surface area excluded from the intervention but kept in the intervention group by intention-to-treat principles to avoid breaking of randomization. Although minors will not be involved in the study, to avoid spillover injury to children in the intervention households, all members of intervention households under the age of 18 will also undergo urine dipstick testing. If proteinuria (as +  + protein on urinalysis) is detected on two separate tests spaced three days apart, the household will be excluded from receiving the LSSS intervention (but followed in the intervention arm to avoid breaking randomization).

Lastly, potential participants (but not households) will be excluded if they have (1) a terminal illness, (2) are substantially mentally disabled (and thus unable to give consent), or (3) are bedridden.

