### Who will take informed consent?

Fieldworkers will provide all potential participants in the study with a consent form to read. The document will contain multiple diagrams and illustrations to explain the key concepts of the project. For illiterate participants, the fieldworkers will read the consent form in the native spoken language of the participants, as necessary. The consent form will outline the scope, purpose, and procedures of the study as well as the risks and benefits of study participation. The fieldworkers will answer any questions before asking for consent. If the potential participant meets the inclusion criteria (and the other members of the household do not meet the exclusion criteria) and wishes to participate, she or he will be asked to sign or thumbprint the consent form; the fieldworker will then countersign. If the participant is illiterate, a witness will sign in addition to the participant’s fingerprint. One signed consent form remains with the participant; a second signed consent form is retained by the study team. All study subjects will be informed that they may withdraw consent to participate in the trial at any point during the study.

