### Recruitment

Given concerns for lower uptake among study participants randomized to the education only arm, we decided to build a conservative estimate approximated from the lowest value of uptake in the literature of free salt substitute of 75% [31, 38]. This would support the selection of a final sample size of 206 participants per study arm, leading to a total study recruitment requirement of 618 subjects. This is well within the 2,181 subjects currently registered within the BRAC cohort described above.

We shall recruit study households in the following stages: (a) the eligible households in the sampling frame will be listed against the inclusion criteria, i.e., households without any diagnosed case of chronic kidney disease (CKD), nephrotic syndrome, or hyperkalemia, no history of current intake of potassium supplement or potassium-elevating medications, and households consisting of at least two adults (aged ≥ 18 years) willing to participate in the trial; (b) from the eligible households, we shall choose a systematic random sample (with an interval of five houses) to create buffers among study households to reduce the chances of spill-over; (c) the systematic random sample of 309 households will be further inflated by the current CKD prevalence of 17.3% in Bangladesh; the resulting 362 households will then undergo the randomization process [39]. We will plan to exclude the households with CKD or nephrotic syndrome cases; to ensure this, we will perform serum creatinine tests among the adults and urine dipstick tests among those under 18 years of age with the exclusion criteria previously enumerated.

The aforementioned recruitment areas of Uttor Basupara, Basupara, and Mondolpara are adjacent to one another and are further divided into six regions. As homes within these regions are not evenly clustered in an area (and do not adhere to a geographic grid with convenient central points of interest), we will designate one end of the area as the starting point. The field workers will use a random number generator to select the first household, then move on to enrolling homes sequentially, maintaining a gap of five households between enrolled homes. This process will be continued until the end of an area is reached.

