### Plans for collection, laboratory evaluation, and storage of biological specimens for genetic or molecular analysis in this trial/future use

Trained specialists will be recruited to collect blood specimens from adults residing in households of the salt-recipient participants. The samples will be stored by the hospital for the period of testing and destroyed once the reports are generated. Serum creatinine tests will be conducted on the collected blood samples.

Urine samples will be collected from children (under 18) residing in households of salt-recipient participants. Trained field workers will perform spot tests, and the samples will be destroyed once the results are recorded. These two tests will be conducted only once before the initiation of the intervention.

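### The on-study rule for stopping the salt watches only the two enrolled participants, although the salt feeds a whole kitchen and the entry rule protects every household member

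*Protocol article*

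**What the plan says.** **Exposure.** Trial design randomizes households and defines a household by its shared kitchen. Intervention description delivers one monthly parcel of low-sodium salt to each household in the free-salt arm.

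**Who participates.** Eligibility criteria invites "One male and one female adult" per household. Other residents eat the same food but are not participants.

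**At entry.**
- The abstract excludes "households with members known to have high serum potassium levels", along with households with the other renal and potassium conditions.
- The consent section requires that "the other members of the household do not meet the exclusion criteria".
- Recruitment lists only households free of known cases and adds "We will plan to exclude the households with CKD or nephrotic syndrome cases", with adult creatinine and child dipstick tests as the means.
- For a minor with repeated proteinuria, Eligibility criteria states that "the household will be excluded from receiving the LSSS intervention", with follow-up continuing in the assigned arm.
- For adults, the same section speaks of those with eGFR "values < 60 ml/min/body surface area excluded from the intervention but kept in the intervention group by intention-to-treat principles".
- The specimen section places creatinine testing among "adults residing in households of the salt-recipient participants" and says: "These two tests will be conducted only once before the initiation of the intervention".

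**During the trial.** The section on discontinuing or modifying interventions stops free salt when a participant develops hyperkalemia or comes to meet an exclusion criterion. The concomitant-care section says that participants who develop such conditions are taken out of the free-salt arm. Neither names any other resident.

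**The concern.** The entry rule and the on-study rule protect different people. The first covers everyone who eats from the kitchen; the second covers the two people whose blood pressure is measured. The hazard, extra potassium for someone with poor renal function or on a potassium-raising drug, does not depend on being enrolled. The protocol accepts this when it tests children, who are not participants, and withholds salt from the whole household if one is positive.

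Suppose an older relative who lives in the home but is not enrolled is diagnosed with kidney disease in the second month. Had this been known at recruitment, the household would not have been listed. Once the trial is running, the text gives no instruction to stop, and a worker who follows it keeps delivering. The section on interim analyses leans on the strictness of the exclusion criteria to justify having no interim safety outcomes, so those criteria should hold for everyone exposed for as long as the salt is supplied.

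A second, smaller matter is wording. Person-level language in the adult eGFR clause, and the verbs for excluding a household or removing a participant from an arm, leave field staff to work out what to do and what happens to the data.

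**Working it through.** This is a comparison of rules. The only arithmetic is a bound on exposure.

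**1. Unit of each rule**

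| Rule | Section | Unit that triggers it | Unit it acts on |
|---|---|---|---|
| Known conditions at entry | Abstract; consent; Recruitment | any household member | household |
| Proteinuria in a minor | Eligibility criteria | any minor | household, followed in its arm |
| Adult eGFR below 60 | Eligibility criteria | any resident adult tested | worded as the person, kept in the arm |
| New condition on study | Discontinuing or modifying; concomitant care | participant only | free-salt provision, or the participant |
| Salt delivery | Intervention description | n/a | household |

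Only the on-study row has a trigger narrower than the household.

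**2. Is the adult eGFR row a separate error?** No. Recruitment says the creatinine tests serve a household exclusion. Eligibility criteria tests all resident adults, which a rule about participants alone would not need. Its next paragraph contrasts participants with households when it lists terminal illness, mental disability and being bedridden, which implies that the preceding criteria act on households. The intent can be recovered; the sentence does not state it.

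**3. Does another section close the on-study gap?** The laboratory tests are done once, before the salt starts, so a later condition becomes known only by report. Adverse event reporting trains staff to elicit and report events and to refer participants for care, but gives no rule for stopping delivery. Interim analyses plans no stopping guideline, and there is no separate data monitoring committee. None of these covers a non-participant.

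**4. Bound on exposure per case.** The timeline marks the free-salt arm at six monthly points. If a condition becomes known just after the first delivery, 6 − 1 = 5 parcels remain; after the second, 6 − 2 = 4. This limits what could be delivered to one such household. It is not an estimate of how often this happens.

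**5. The plan's one figure on renal exclusion.** Recruitment inflates 309 households by 17.3%: 309 × 1.173 = 362.5, stated as 362. It reproduces. It is a recruitment allowance for disease present at baseline and says nothing about new conditions in follow-up, so it cannot size the gap.

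**The case against.** **The gap is small and perhaps covered elsewhere.** Known cases in any member are screened out at entry, and resident adults and minors in salt-recipient households are tested. What remains is a condition newly known in a non-participant within six months. Stopping free provision can fairly be read as stopping the household's parcel, since that is how salt is delivered. Staff visit monthly and are trained to report adverse events, and a full protocol may say more than the article. Most of this is fair and limits the weight of the point. But reading the action as household-wide does not widen the trigger, which remains a participant. The article states the trigger, so this is a rule set too narrowly and not a detail left out.

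**A stronger reading a reader might infer: one-sided exclusion after randomization.** Recruitment randomizes 362 households and then speaks of excluding those with kidney disease, and testing is described for salt recipients. One could compute 362 − 309 = 53 households, 53/3 = 17.7 per arm, and arms of about 103 (120.7 − 17.7), 121 and 121. The documents do not support this. The Recruitment text refers back to criteria already listed, and under those an excluded person or household gets no salt but stays in the assigned arm. The retention section collects outcomes from those who discontinue, and the statistical section analyses as randomized. The split would also need a test yield equal to the planning allowance.

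**Another tempting figure.** Taking the five adults per cluster in Sample size as residents would give 5 − 2 = 3 of 5 adults outside the trigger. That five is a power input and not a stated household size, so the count is not used.

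**Conclusion.** The point holds for the on-study trigger. The protocol guards every household member at entry, but once delivery has begun only two named adults can stop it. Followed as written, the rule would keep potassium salt going to a kitchen where another resident is newly known to have kidney disease, hyperkalemia or a potassium-raising treatment.

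This is a matter of participant safety and internal consistency. It does not show bias in the primary comparison. Its frequency cannot be derived from the documents; per case it is bounded by five remaining parcels. No arm-size imbalance, count of affected residents or loss in mm Hg is claimed. The conclusion assumes only that participant means an enrolled adult, as Eligibility criteria uses the term, and that no unshown operating procedure already widens the trigger.

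The adult eGFR wording and the verb in Recruitment are clarifications of an intent the document already shows. Keeping affected people in their randomized arm is sound and should stay. The change should be made, because it is cheap and concerns people who are exposed without being enrolled.

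**What to change.** **Main change**, in the sections on discontinuing interventions and on concomitant care:
- Make the trigger any household member known to have developed an exclusion condition, as reported at the existing monthly visits.
- Replace removal from the arm with: *LSSS delivery to the household stops, and its participants are followed and analysed in the randomized arm.*

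**Two edits for consistency:**
- Eligibility criteria, adult clause: *If any resident adult in a free-LSSS household has eGFR < 60, the household receives no LSSS but is followed and analysed in its randomized arm.* This matches the clause for minors.
- Recruitment: say that LSSS is withheld from households with CKD or nephrotic syndrome, in place of saying that they are excluded.

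**Cost.** No new test or visit; the monthly visit must include asking about new diagnoses and medicines in all residents. A few more households in the salt arm may stop salt, which dilutes the intention-to-treat contrast slightly, by an amount the documents do not fix. Undiagnosed disease will still be missed, because the laboratory tests are not repeated.

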## Sample size

Assuming a Type I error rate of 0.05 and a desired power of 0.80 for our study, we hypothesize an intervention effect of 2.0 mm of mercury (mm Hg) of systolic blood pressure reduction with standard deviation of 20.0 mm Hg. These values were extrapolated from prior RCTs of low-sodium salt interventions in LMICs, whose effect sizes have varied from 1.1 to 10 mm Hg (with variance around the order of 20–30 mm Hg) with most studies finding effect sizes of over 3.0 mm Hg in blood pressure reduction [30–37]. Uptake of the intervention in these studies ranged from 74.3 to 94.1%.

Assuming an analysis of simple difference of outcome, a conservative intra-cluster coefficient (ICC) of 0.25 (and an expected cluster membership of five adults per cluster), we estimated an average of 33 clusters would be necessary per study arm to detect an effect size of our proposed magnitude. This would suggest that a total enrollment of 660 study subjects would be needed for our study.

Below, a table (generated from the National Institutes of Health Sample Size Calculator for GRTs [group- or cluster-randomized trials]) noting the absolute detectable difference (in millimeters of mercury) for a range of cluster sizes by cluster numbers is presented:
[figure not shown]

Of note, we will be obtaining blood pressure measurements at baseline. Thus, having the correlation between baseline and endline BP will provide additional power over this very conservative estimate.

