Standard errors will be adjusted for clustering using the robust sandwich estimator. *P*-values < 0.05 will be considered statistically significant for the purpose of hypothesis testing for the primary analysis. *P*-values < 0.05 will be considered statistically significant for secondary analyses of binary outcome variables. All primary and secondary analyses will be conducted “as randomized” (i.e., following the intention-to-treat principle).

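### The CKD inflation from 309 to 362 households does not offset the dilution that arises when the same households stay, without LSSS, in the intention-to-treat analysis

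*Protocol article*

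**What the plan says.** All of this is in the protocol article.

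- **Sample size** plans for an "intervention effect of 2.0 mm of mercury (mm Hg) of systolic blood pressure reduction with standard deviation of 20.0 mm Hg", with 5% type I error and 80% power. It reports for the source trials: "Uptake of the intervention in these studies ranged from 74.3 to 94.1" per cent.
- **Recruitment** gives the CKD step: "the systematic random sample of 309 households will be further inflated by the current CKD prevalence of 17.3% in Bangladesh". The resulting 362 households are randomised. The same paragraph says that households with CKD or nephrotic syndrome are to be excluded, on the basis of creatinine and dipstick tests.
- **Eligibility criteria** says that adults with eGFR below 60 are "excluded from the intervention but kept in the intervention group by intention-to-treat principles to avoid breaking of randomization". A household with a child who has confirmed proteinuria is likewise not given LSSS but is followed in its arm.
- **Plans for collection, laboratory evaluation, and storage of biological specimens** places the testing in households of salt recipients.
- **Plans to promote participant retention and complete follow-up** collects all outcomes from people who discontinue or deviate. **Statistical methods** analyses everyone as randomised, "following the intention-to-treat principle", and the section on non-adherence and missing data repeats this.

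No section lowers the 2.0 mm Hg for people in the LSSS arm who do not receive LSSS.

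**The concern.** Adding participants repairs the loss of people from an analysis: the effect is unchanged and only the count falls. It does not repair non-receipt among people who stay in the analysis, because they lower the average difference itself. If a fraction f of the arm is treated and the rest gain nothing, the difference becomes f times the planned one, and the sample must grow by 1/f² to hold power. The plan uses the first remedy for what its Eligibility criteria and analysis rules turn into the second problem.

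Two of the three planned comparisons involve the LSSS arm: against control and against education only. For both, the difference to be expected would be smaller than the one used for sizing. A null result would then be judged against 2.0 mm Hg when the trial was aimed, in effect, at something less.

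**Working it through.** **Inputs.** From Sample size: difference 2.0 mm Hg, alpha 0.05 (two-sided assumed; the text does not say), power 0.80. From Recruitment: 309 households, 17.3%, 362 households. Cluster size and ICC are held fixed, so information is proportional to the number of households.

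**Step 1, the plan's figure.** 309 x 1.173 = 362.5, stated as 362. The step is therefore a linear increase. The usual form for people who leave would be 309 / 0.827 = 374.

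**Step 2, kept and untreated.** Take 17.3% as the share of the LSSS arm not given LSSS, with no gain among them, so f = 0.827.

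- Expected difference: 2.0 x 0.827 = 1.65 mm Hg.
- Equivalent fully treated households: 362 x 0.827² = 248, against 309.
- Relative power, if 309 fully treated households gave 80% (1.96 + 0.84 = 2.80): 2.80 x 0.827 x sqrt(362/309) = 2.51, and 2.51 - 1.96 = 0.55, which is about 71%.
- With 374 households: 2.80 x 0.827 x sqrt(374/309) = 2.55, about 72%.
- Households needed to hold 80%: 309 / 0.827² = 452.

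**Step 3, range for the effect kept by the untreated.** If they keep a share k of the effect, the multiplier is 0.827 + 0.173k.

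| k | multiplier | relative power |
|---|---|---|
| 0 | 0.827 | about 71% |
| 0.25 | 0.870 | about 75% |
| 0.50 | 0.914 | about 79% |

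**Step 4, range for the untreated share.** Halving the share to 8.65% gives f = 0.914, the same 79% as the last row. In the other direction, if 17.3% is a per-person figure, cases are independent and one affected adult bars a two-adult household, the share is 1 - 0.827² = 31.6%. Then f = 0.684, the difference is 1.37 mm Hg, and 2.80 x 0.684 x sqrt(362/309) = 2.07, about 55%.

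**Step 5, the other reading (excluded).** 362 x 0.827 = 299 households would remain, still below 309. If exclusion touched only the LSSS arm, that arm would keep 362/3 x 0.827 = 99.8 of its planned 103. That is a small shortfall, but it would come from removals after randomisation in one arm, against the as-randomised rule.

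**Step 6, absolute power.** With 362/3 x 2 = 241.3 participants per arm and a design effect of 1 + (2 - 1) x 0.25 = 1.25, the standard error is sqrt(2 x variance x 1.25 / 241.3). Going from 2.0 to 1.65 mm Hg:

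- SD 20 as stated: from 17% to 13%.
- Variance 20, the reading that reproduces the stated 33 clusters: from 99% to 95%.

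**Step 7, baseline adjustment.** Adjusting for baseline multiplies the variance by about 1 - r². Offsetting 248 against 309 needs 1 - r² = 0.80, so r is about 0.45. The protocol gives no correlation.

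**The case against.** Several points on the other side stand, and they limit the finding.

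- **Recruitment says CKD households are excluded.** A linear top-up fits that wording in kind. But it contradicts Eligibility criteria, and step 5 shows that 362 falls short on that reading too.
- **No effect in the untreated is an assumption.** The LSSS arm also includes education, and the protocol does not say that people barred from LSSS lose it. Against control, step 2 is therefore an upper bound on dilution for the assumed share. Against education only, no added effect is the natural assumption.
- **17.3% may not be the untreated share.** Diagnosed CKD is removed when households are listed, which lowers it. Several adults per household raise it.
- **The 2.0 mm Hg may already be discounted.** The source trials had incomplete uptake, and most are said to have found more than 3.0 mm Hg. The protocol does not say whether 2.0 is an intention-to-treat figure.
- **Baseline adjustment could absorb the loss** at a correlation of about 0.45. Sample size presents it as extra power and gives no value.

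A reader might also infer that the 75% uptake allowance compounds with the CKD share, giving 2.0 x 0.75 x 0.827 = 1.24 mm Hg, or that uptake alone cuts power to about 65% (165 raised to 206 per arm). The text does not support this. Recruitment says "we decided to build a conservative estimate approximated from the lowest value of uptake in the literature of free salt substitute of 75" per cent, and gives as its reason the concern about the education-only arm, whereas the CKD bar concerns LSSS. The step from 165 to 206 is itself only inferred (165 x 1.25 = 206.25). Both figures are hypothetical.

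**Conclusion.** The point holds for the CKD step. The plan tops up households linearly while its Eligibility criteria and analysis rules keep the untreated in the LSSS arm, and nothing reduces the 2.0 mm Hg. On the plan's own 17.3% and no gain among the untreated, the target difference is about 1.65 mm Hg and the relative power about 71% of a nominal 80% design; it is about 79% if half the effect is kept. The range is wide because both the untreated share and the retained effect are unknown.

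It would be tempting to say that the trial's power falls from 80% to 71%. The documents do not support that. The stated SD of 20 gives no 80% to begin with, while reading 20 as a variance leaves 95% after the CKD dilution. The phrase "whose effect sizes have varied from 1.1 to 10 mm Hg (with variance around the order of 20–30 mm Hg" leaves that question open, and it is a separate and larger problem. What does not depend on it is the loss of information, 248 against 309 households, under the assumptions of step 2.

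**What to change.** 1. Reconcile Eligibility criteria and Recruitment on whether households with CKD, low eGFR or a proteinuric child are kept in the arm or excluded. Use one wording in both.
2. Keep the intention-to-treat analysis and the planned enrolment.
3. In Sample size and Recruitment, restate the target difference and the power at 362 randomised households on the intention-to-treat effect, instead of relying on the linear inflation. Give a range for the share not given LSSS and for the effect they keep, and state any baseline correlation assumed.
4. State whether the 2.0 mm Hg is already an intention-to-treat figure from trials with 74.3 to 94.1% uptake. If it is, drop the 75% allowance. If not, apply the allowance to the effect in the arm it concerns, which Recruitment names as education only.

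The cost is protocol wording and one recalculation, with no change to enrolment or analysis. The stated power may become less favourable.
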